### Ethics/governance

The study received favorable ethical approval from the local Research Ethics Committee (REC), Queen Square, number 14/LO/0748. Sponsorship is provided by the R and D department at UCLH NHS Foundation Trust. A trial steering group consisting of the CI, academic supervisors, expert patients, statistician, expert in qualitative methodologies, consultant neurosurgeon and the interventional physiotherapists will meet bi-annually. Annual reporting of trial progress will be submitted to the REC and the funding body (National Institute for Health Research, NIHR). Adverse events will be reported to the CI for action in accordance with the defined stopping rules.

### Surgical procedures

All surgery will be performed by a member of the Complex Spine Team at NHNN. The surgical approach will be entirely at the discretion of the attending surgeon. In all cases however, this will involve rigid instrumentation, with or without surgical decompression of the relevant nerve roots/central canal. Records will be kept for reporting of the exact surgical procedure utilised.

### Randomisation and blinding

It is not possible to blind subjects to their allocation. Randomisation to either RG or UC will be by block randomization, utilising codes generated independently by the trial statistician at the Faculty of Health and Social Care Sciences, St Georges University of London (HEI). Concealment of allocation will be achieved by the remote generation of codes and the use of sealed opaque envelopes, numbered sequentially.

### Immediate postoperative care

Following LFS both groups will remain in hospital for approximately 5 days, experiencing identical care, including early ambulation, (usually within 6 h of the operation), check radiographs, wound monitoring, pain control, routine nursing observations, physiotherapy mobility check/advice and antithrombotic exercises.

The standard advice given to all patients following LFS in our unit is to avoid heavy lifting (nothing more than a kettle) for 3 months. This allows wound healing and encourages consolidation of the osseous fusion. During this period patients are encouraged to gradually increase their outdoor mobility with short regular walks to a maximum of 2 miles/day. All subjects will follow this standard advice for the first 3 months following surgery, irrespective of group allocation. A check appointment 6 weeks postoperatively with the surgical team monitors recovery.

At 3 months following surgery, if the surgical team is satisfied with the technical aspects of the surgery (no indication of infection, loosening of the metal ware, or unexpected symptomology) participants will commence treatment according to their randomisation group (RG or UC).

### Development of the rehabilitation programme

The rehabilitation programme described in this protocol was developed by the CI in collaboration with the department of Physiotherapy UCLH, the Complex Spine Surgical Team (NHNN), and the study supervisors. The limited published studies suggest a potential benefit with complex rehabilitation over conventional exercise therapies [21, 22]. It was felt patients undergoing LFS had multi-dimensional needs [25] in keeping with the biopsychocosocial model of back pain [27]. This study will go some way to advancing the understanding of the needs of this patient group highlighted as urgent in a recent systematic review [24]. The rehabilitation protocol described is designed to optimise recovery through the provision of individualised, progressive exercise, education and peer support, employing principles of cognitive behavioural therapy (CBT) to help overcome maladaptive health beliefs.

In planning the current feasibility study a small-scale local exploratory study [26] was conducted. Compliance, willingness to participate and clinical outcomes were good which warranted the further evaluation described in this protocol.

### Rehabilitation group content

RG consists of 10 consecutive weekly outpatient appointments (maximum 90 min), including structured advice, progressive exercise and peer support. The delivery of the RG will employ principles of CBT, include a maximum of eight participants and be run in the physiotherapy gymnasium at UCLH, supervised by a senior physiotherapist with more than 10 years of experience of this subject group. All staff providing the RG will receive a minimum of 3 h of training in the delivery of the intervention.

The overarching aim of the RG is to provide clear, consistent educational messages, progressive physical rehabilitation (including home exercise) using low-tech exercises not requiring complex equipment or supervision with peer support. Each RG will commence with an initial, brief education session as outlined in Fig. 2. This is followed by an individualised, progressive exercise regime supervised by the therapist concluding with a monitored peer support session.

**Fig. 2 Fig2:**
[figure not shown]
Rehabilitation protocol overview

#### Education component

This comprises of five brief pre-planned educational sessions (maximum 20 min duration), conveying clear and concise principles relating to improving physical function and managing pain, beginning with topic 1 and progressing to topic 5. This includes topics such as the benefits of exercise, pacing, pain mechanisms, hurt≠harm and the over-/under-activity cycle to correct maladaptive beliefs and thus facilitate recovery, possibly via cognitive restructuring and *in vivo* exposure learning [28–30]. Topics will be briefly explored within the personal experience of the participants and open discussions will be encouraged. Each session will commence by revisiting the topic(s) from the previous week. In this way the educational component builds as participants recover lost function. After the first 5 weeks each topic is revisited to help participants apply the early-learned principles into their functional recovery.

#### Exercise component

This comprises an individualised, progressive, physical rehabilitation programme with exercises aimed at improving cardiovascular function, limb and spinal strength and flexibility. Assistance will be given as required. The selected exercises are intentionally low-tech and do not require complex equipment or supervision; as such they can easily be replicated outside the hospital. Records of training volume/intensity will be kept. Weeks 1 to 3 comprise the familiarisation phase allowing participants to become acquainted with the gym environment and post exercise symptom response. Following this the exercise load will be progressed according to individual ability. Exercise diaries to record activity between groups, problems or post exercise symptom change will be provided and reviewed weekly to monitor progress and compliance for reporting.

#### Peer support component

A peer-led discussion will be held at the end of each session (maximum 20 min duration) during which participants will be encouraged to discuss common problems and work towards identifying solutions based on shared experience. The physiotherapist will monitor this discussion to ensure no reinforcement of maladaptive beliefs and identify any psychosocial blocks to recovery.

### Usual care arm

This will include the same postoperative advice that all participants receive in that they should steadily, self-progress their walking mobility up to a maximum of 2 miles per day. The provision of subsequent physiotherapy, analgesia or pain management services will be entirely at the discretion of the surgical team or GP. Participation in this study will not preclude the provision of any rehabilitation that is deemed necessary; rehabilitation requirement will be recorded and reported.

### Primary and secondary outcome measures

Primary outcome measures include a range of markers evaluating the feasibility of the protocol, specifically the recruitment process, compliance and acceptability, as follows. For the recruitment process these will be the numbers of: eligible patients; patients who accept the PIS (following phone contact from the CI); patients willing to discuss trial participation (with the CI at PAS), and participants who provide consent and BLD. For compliance these will be: the rehabilitation intervention (review of exercise diaries and attendance); usual care (attendance at other rehabilitation settings/type of rehabilitation provided); the trial protocol, and the rate of/reasons for attrition. For the acceptability of the rehabilitation group and UC this will be qualitative evaluation to better understand participants’ perceptions of surgical after care in RG and UC.

The secondary evaluation utilises a cluster of quantitative outcome measures. The differences between groups will be investigated taking into account the variation between patients and the longitudinal nature of the data, using such methods as repeated measures analysis of variance (ANOVA) or multilevel regression as appropriate. The longitudinal approach will allow us to use all observations even if a patient is lost to follow up. The observed effect size and inter-patient variance will allow us to propose a suitable sample size for future research. The measures include: the Oswestry disability index (ODI), which measures self-reported level of disability [31]; the aggregated functional performance test (AFPT), which is the aggregated time (in seconds) for the subject to sit-to-stand, walk 50 yards, and make a stair ascent/descent, to quantify the level of physical function [32, 33]; the pain self-efficacy questionnaire (PSEQ), which measures self-reported ability to self-manage pain [34]; the hospital anxiety and depression scale (HADS), a measure of hospital-related level of anxiety and depression [35]; the European quality of life-5 dimensions (EQ-5D) measure of health-related quality of life across a range of indicators [29], and the client services receipt inventory (CSRI), an economic questionnaire customised to the patients’ needs post LFS [36].

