### Participants (inclusion and exclusion criteria)

A convenience sample of subjects (n = 50) will be recruited from the Neurosurgical Department of the National Hospital for Neurology and Neurosurgery, (NHNN, UCLH, NHS Foundation Trust). The Complex Spine Team at NHNN performs approximately 60 fusion procedures per annum. If 33 % of these patients are eligible and consent, we will meet our recruitment target in 30 months. A local exploratory study suggested this recruitment strategy is achievable; contingency plans are in place should recruitment prove inadequate. A study overview is shown in Fig. 1.

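### RG is delivered in groups, but the inputs named for the RG–UC comparison and for sizing the next trial make no allowance for clustering in that arm

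*Protocol article*

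**What the plan says.** Individuals are randomised (protocol article, Randomisation and blinding: "Randomisation to either RG or UC will be by block randomization"). After that, only one arm is grouped.

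- **RG.** Ten weekly sessions which, according to Rehabilitation group content, "include a maximum of eight participants and be run in the physiotherapy gymnasium at UCLH, supervised by a senior physiotherapist". Under Peer support component, each session closes with a discussion in which "participants will be encouraged to discuss common problems and work towards identifying solutions based on shared experience".
- **UC.** Under Usual care arm, any further physiotherapy or pain management is left to the surgical team or GP. There are no trial groups.
- **Analysis.** Under Primary and secondary outcome measures, the arms are compared "taking into account the variation between patients and the longitudinal nature of the data", by repeated measures ANOVA or multilevel regression, whichever is appropriate.
- **What is carried forward.** The same section states: "The observed effect size and inter-patient variance will allow us to propose a suitable sample size for future research".

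The article nowhere mentions a rehabilitation-group or therapist term, an ICC or a design effect. The items listed under Data collection do not include group membership.

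**The concern.** Patients in one RG group share sessions, peers and a therapist, and the peer exchange is meant to be an active part of the treatment. Their outcomes after the programme may therefore be correlated, while those of UC patients are not correlated in this way. This is a partially nested design. An analysis in which the patient is the only cluster then gives a standard error for RG minus UC that is too small.

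The consequence for these 50 patients is limited, because the comparison is secondary and the Discussion says that the trial is not designed to show efficacy. The consequence for the next trial matters more. Aims and objectives and Discussion both promise a robust basis for later efficacy work. A sample size built from the two named inputs has no factor for the grouping.

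**Working it through.** **The plan's own figure.** The sample size rests on recruitment (Participants section): "A convenience sample of subjects (n = 50) will be recruited", from a team that "performs approximately 60 fusion procedures per annum". The section adds: "If 33 % of these patients are eligible and consent, we will meet our recruitment target in 30 months". Check: 60 × 0.33 × 30/12 = 49.5, against 50. The figure reproduces, and clustering does not touch it.

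**Likely group size.** The allocation ratio is not stated. Assuming 1:1, there are 25 RG patients over 30 months, or 25/30 = 0.83 per month. A ten-week course lasts 10/(52/12) = 2.31 months, so about 0.83 × 2.31 = 1.9 RG patients accrue per course. Accruing 8 takes 8/0.83 = 9.6 months. RG starts after the 3-month review, lasts ten weeks, and is followed by the 6-month assessment, so there is little room to wait for a group to fill. Groups of 2 to 4 trial patients are plausible here, allowing for uneven accrual or some batching. Eight is the stated maximum, which a larger trial might reach.

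**Formulas.** Let m be the RG group size, with equal arms and equal total variance.

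- RG design effect: DE = 1 + (m − 1) × ICC. For UC it is 1.
- Ratio of the true variance of the difference to that under independence: V = (1 + DE)/2.
- Ratio of standard errors: √V.
- True size of a nominal two-sided 5% test: 2Φ(−1.96/√V).
- True power of a trial planned for 90% without allowance: Φ(3.2415/√V − 1.96), where 3.2415 = 1.96 + 1.2815.

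The ICC range of 0.01 to 0.10 and the 90% power are assumptions; the article gives neither.

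| m | ICC | DE | V | √V | Size of 5% test | Power |
|---|---|---|---|---|---|---|
| 2 | 0.01 | 1.01 | 1.005 | 1.002 | 5.1% | 90% |
| 2 | 0.05 | 1.05 | 1.025 | 1.012 | 5.3% | 89% |
| 2 | 0.10 | 1.10 | 1.050 | 1.025 | 5.6% | 89% |
| 4 | 0.01 | 1.03 | 1.015 | 1.007 | 5.2% | 90% |
| 4 | 0.05 | 1.15 | 1.075 | 1.037 | 5.9% | 88% |
| 4 | 0.10 | 1.30 | 1.150 | 1.072 | 6.8% | 86% |
| 8 | 0.01 | 1.07 | 1.035 | 1.017 | 5.4% | 89% |
| 8 | 0.05 | 1.35 | 1.175 | 1.084 | 7.1% | 85% |
| 8 | 0.10 | 1.70 | 1.350 | 1.162 | 9.2% | 80% |

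**Simulation check.** An unclustered t-test was simulated with 25 patients per arm and 40,000 runs. At ICC 0.01, 0.05 and 0.10, RG groups of 7, 6, 6 and 6 give a true size of 5.4%, 6.4% and 8.0%. Groups of 3 to 4 give 4.9%, 5.7% and 6.4%. This agrees with the formulas to within a few tenths of a percentage point.

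**Next trial, as an illustration.** For an assumed effect of 0.5 SD, 90% power and 5% two-sided, 2 × 3.2415²/0.25 = 84.06, so 85 per arm if clustering is ignored. Multiplying 84.06 by V for groups of 8 and rounding up gives 88, 99 or 114 per arm at ICC 0.01, 0.05 or 0.10. Keeping equal arms and multiplying both by V, or keeping UC at its size and multiplying RG by DE, gives the same total apart from rounding. Both restore the planned power.

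**The case against.** A reader might infer that the plan definitely ignores clustering and that its standard errors are definitely too small. The document does not support that.

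- **The list is open.** The text does not say that patients and time are the only sources of variation. Multilevel regression could hold a group level, and random-effects structure is commonly left to an analysis plan, which is not shown. This stands against the strong reading. It does not remove the point, because the article itself names the sources to be modelled and the variance to be carried forward, and neither covers the treatment group.
- **The ICC is unknown.** Exercise is individualised and partly done at home, which weakens within-group correlation. If one physiotherapist led every group, the therapist would add no variance between groups. The article speaks of one supervising physiotherapist in one place and of several staff in others, so this is unclear. Shared peers remain either way.
- **The largest figures pair extremes.** A power of 80% and a test size of 9.2% need both the maximum group size and the highest assumed ICC. This stands: in this trial the distortion is probably small.
- **The SD carried forward is nearly sound.** The spread between RG patients already absorbs most of the variation between groups. This also stands. What is missing is the design-effect multiplier, and the article does not rule out adding one.
- **A group effect is barely estimable here.** With about 25 RG patients this is true, and it limits the fix: a random group effect cannot carry the main analysis or yield a usable ICC.

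**Conclusion.** The point holds in a conditional and modest form. The inputs that the article names make no allowance for clustering in the RG arm. If the ICC is positive, following them understates the uncertainty of the secondary 6- and 12-month comparisons and the size of the next trial.

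Over an assumed ICC of 0.01 to 0.10, groups of 2 to 4 mean a standard error too small by a factor of about 1.00 to 1.07. Groups of 8 would raise the factor to between 1.02 and 1.16, and the required total for the next trial by 3.5% to 35%. The group-size range rests on 1:1 allocation and even accrual.

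Baseline and 3-month data precede RG and are untouched. So are the primary feasibility outcomes and the target of 50. The change is worth making mainly for the sample size that this trial is meant to inform.

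**What to change.** 1. Record the rehabilitation group or cohort, and the therapist, for every RG participant. If entry is rolling, keep the session dates so that shared attendance can be reconstructed. Recruitment was only starting (Trial status), so this can be done prospectively.
2. For the 6- and 12-month outcomes, report a partially nested model as a sensitivity analysis: a random group effect in RG only, a patient effect in both arms, and small-sample degrees of freedom.
3. State that the future sample size will multiply the RG arm by 1 + (m − 1) × ICC over an assumed range such as 0.01 to 0.10. Here m should be the group size planned for that trial. This trial's ICC point estimate should not be used, since so few groups cannot estimate it usefully.

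The cost is one or two data fields and a few sentences of analysis wording. The downside is slightly wider intervals in the sensitivity analysis and a somewhat larger proposed future trial.

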### Aims and objectives

The aim of this study is to evaluate the feasibility of providing complex rehabilitation in a group setting 3 months after technically successful instrumented LFS. This will include an analysis of our recruitment strategy, compliance with the study protocol and rehabilitation intervention. It will also evaluate the acceptability and characteristics (including population mean, SD and effect size) of a cluster of quantitative outcome measures. This will help achieve a more detailed analysis of the patient group under evaluation and thus a robust basis for the analyses of future work evaluating clinical efficacy. The nested qualitative analysis will identify strengths and weakness of the proposed protocol. This study will provide useful data for the development, refinement, and analysis of complex rehabilitation following instrumented LFS.

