## Discussion

It is anticipated that this study will evaluate the feasibility of providing complex, structured, progressive rehabilitation 3 months following technically successful LFS. We anticipate demonstrating that this is feasible. We expect participants to be compliant with the rehabilitation intervention. We also expect the qualitative analysis to demonstrate satisfaction amongst participants in the RG. This trial is not designed to demonstrate clinical efficacy, however, we expect evidence of reduced disability (ODI) amongst participants receiving RG compared with UC. We will report on the characteristics (including population mean, SD and effect size) to help achieve a detailed analysis of the patient group and thus a robust framework for the development of future studies evaluating clinical efficacy.

We aim to achieve a better understanding of the rehabilitative requirements of participants following LFS and a mechanism by which rehabilitation to address those needs may be robustly analysed, allowing us to shape future trials to optimise recovery. A dissemination plan including publication in open access peer-reviewed journals following the CONSORT principles [41] and conference presentations is in place.

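### The effect observed in 50 patients is too imprecise to set the size of the next trial; the SD, attrition and recruitment rates are usable

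*Protocol article*

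**What the plan says.** The section on primary and secondary outcome measures makes feasibility primary and treats the quantitative measures as a secondary evaluation. On the use of that evaluation it says: "The observed effect size and inter-patient variance will allow us to propose a suitable sample size for future research". Two inputs to future sizing are therefore named, the between-group effect and the between-patient variance.

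The aims list the "characteristics (including population mean, SD and effect size) of a cluster of quantitative outcome measures" among the things to be evaluated, as a basis for later efficacy work, and the Discussion repeats this. The Discussion also disclaims any design for efficacy, but adds that "we expect evidence of reduced disability (ODI) amongst participants receiving RG compared with UC".

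The sample size comes from throughput: "A convenience sample of subjects (n = 50) will be recruited", "The Complex Spine Team at NHNN performs approximately 60 fusion procedures per annum", and "If 33 % of these patients are eligible and consent, we will meet our recruitment target in 30 months". The randomisation section says "Randomisation to either RG or UC will be by block randomization" and gives no ratio.

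**The concern.** A two-arm trial of this size estimates an SD tolerably well and a between-group effect poorly. Required sample size varies with the inverse square of the planning effect, so error in the effect is magnified in the proposed n. A chance high estimate gives a definitive trial that is too small. A chance low estimate gives one that is needlessly large or impossible to run. Sizing future research is a stated product of this trial, so the choice of input matters even though none of the primary feasibility outcomes depends on it.

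This is more than detail left to a fuller document. The article itself names the effect as a sizing input.

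**Working it through.** **The plan's own figure.** 60 procedures per year × 0.33 × 2.5 years = 49.5, which reproduces the target of 50. The figure is one of throughput and carries no precision argument for a between-group effect.

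**Inputs.** From the article: n = 50, two arms. Assumed, because the article does not give them: 1:1 allocation (25 per arm), true d of 0.3, 0.4, 0.5 or 0.8 SD, two-sided alpha 0.05, next trial planned at 90% power, and an unadjusted comparison at one time point.

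**Precision of the observed effect.** SE(d) ≈ √(2/25) = 0.283. With 48 degrees of freedom the 95% half-width is 2.011 × 0.283 = 0.57. The exact noncentral t range at true d = 0.4 is −0.16 to 0.99.

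**What this does to n.** Per arm, n ≈ 2(1.960 + 1.282)²/d² = 21.0/d². At d = 0.4 this is 131, or 133 with the t correction. At the upper limit, 0.99, it is about 23 with the t correction. At the lower limit it is undefined. At an observed d of 0.05 it is 21.0/0.0025 = about 8,400 per arm, which is not feasible.

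**True power of the next trial.** If n is set from the observed d, the next trial has true power below 80% when the observed d exceeds the true d × (1.960 + 1.282)/(1.960 + 0.842) = 1.157 × true d. It has true power below 50% when the observed d exceeds the true d × 3.242/1.960 = 1.654 × true d. By the normal approximation the chances are 1 − Φ(0.157d/0.283) and 1 − Φ(0.654d/0.283). At d = 0.4 these are 1 − Φ(0.22) = 41% and 1 − Φ(0.92) = 18%. The chance of an observed d at or below 0.05 is Φ((0.05 − d)/0.283), which at d = 0.4 is Φ(−1.24) = 11%.

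| Assumed true d | True power < 80% | True power < 50% | Observed d ≤ 0.05 |
|---|---|---|---|
| 0.3 | 43% | 25% | 19% |
| 0.4 | 41% | 18% | 11% |
| 0.5 | 39% | 13% | 6% |
| 0.8 | 32% | 4% | under 1% |

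The closed forms above and the noncentral t agree with this table to within about two percentage points. The first two columns are chances over all possible results of this trial, including those that give no usable n.

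**Sensitivity.** With 20 per arm (an assumed 20% loss) and true d = 0.4, the three chances become about 43%, 21% and 13%. Baseline adjustment helps little. Planning at 80% power with true d = 0.3, and counting only trials with a positive observed effect, the share of next trials below 80% power goes from 59% to 56% at a baseline correlation of 0.5, and the share below 50% from 38% to 35%.

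**Contrast with the SD.** With 48 degrees of freedom the 95% range for the SD is 0.83 to 1.25 times the estimate. The upper one-sided 80% limit is √(48/39.62) = 1.10 times the estimate. Since n varies with SD², planning on it adds 1.10² − 1 = 21% to n. That error can be bounded and paid for; the error in the effect cannot.

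**The case against.** The sentence says only that the two quantities will allow a size to be proposed. It gives no formula and does not exclude an interval, shrinkage or an important difference set out in a fuller protocol. That stands as far as it goes: the absence of a stated safeguard is not held against the article. What remains is that the sentence names the observed effect as an input, and it is the wrong one.

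The figures depend on assumptions the article does not make, and the problem eases as the true effect grows. That also stands. At d = 0.8 only about 4% of next trials fall below 50% power. Even there about a third fall below 80%.

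The planned longitudinal analysis would be more precise than the single-time-point comparison used here, to the extent that the measures correlate. The gain from baseline adjustment shown above is too small to change the conclusion.

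Reporting an effect estimate is legitimate, so the statement in the aims is not itself at fault.

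Three stronger readings are tempting, and the document does not support them:

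- A reader might infer that a chance null would wrongly end development. The article has no stop/go rule tied to the effect. The last column of the table gives only the chance that no feasible size results.
- A reader might take the Discussion's expectation of reduced disability as a planned efficacy claim. It sets no test or decision rule and follows an explicit disclaimer.
- A reader might conclude that 50 patients is too few. For feasibility outcomes and an SD, nothing here shows that.

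**Conclusion.** The point holds in a limited form. As written, the plan lets the observed effect help set the size of future research, and with about 25 per arm that effect is too imprecise for the purpose. Over assumed true effects of 0.3 to 0.8 SD, a next trial planned at 90% power from the observed effect has roughly a one-in-three to two-in-five chance of true power below 80%. The smaller the true effect, the greater the risk of severe under-powering. These figures rest on 1:1 allocation, an unadjusted single-time-point comparison and assumed true effects.

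The use of the variance, the sample of 50 and the reporting of an effect estimate are not at fault. The conduct of this trial and its primary feasibility outcomes are unaffected, and the correction can be made before any comparison is seen. It should be fixed, but the trial does not turn on it.

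**What to change.** Replace the sentence on future sample size with wording such as:

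> The definitive trial will be sized on a pre-stated minimally important difference in its chosen primary outcome (for example ODI), using the SD from this trial with an allowance for its error (for example the upper 80% confidence limit, about 1.10 times the observed SD), and the observed attrition and recruitment rates. The observed between-group difference will be reported with its 95% CI and will not be used as the planning effect.

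The 80% limit is one convention among several; what matters is that some allowance is stated in advance. ODI is likewise only an example, since the article does not name the primary outcome of the later trial.

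The cost is wording. No extra patients, visits or data are needed in this trial. The proposed future sample size becomes somewhat larger, by about 21% with the 80% limit compared with using the observed SD unadjusted.
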